## Abstract

**Background:**

This currently recruiting randomized controlled trial investigates the effects of integrating components of Emotion-Focused Therapy (EFT) into Psychological Therapy (PT), an integrative form of cognitive-behavioral therapy in a manner that is directly mirroring common integrative practice in the sense of assimilative integration. Aims of the study are to understand how both, an existing therapy approach as well as the elements to be integrated, are affected by the integration and to clarify the role of emotional processing as a mediator of therapy outcome.

**Methods:**

A total of 130 adults with a diagnosed unipolar depressive, anxiety or adjustment disorder (seeking treatment at a psychotherapy outpatient clinic) are randomized to either treatment as usual (PT) with integrated emotion-focused components (TAU + EFT) or PT (TAU). Primary outcome variables are psychopathology and symptom severity at the end of therapy and at follow up; secondary outcome variables are interpersonal problems, psychological wellbeing, quality of life, attainment of individual therapy goals, and emotional competency. Furthermore, process variables such as the quality of the therapeutic relationship are studied as well as aptitude-treatment interactions. Variables are assessed at baseline, after 8 and 16 sessions, at the end of therapy, after 25 ± 3 sessions, and at 6, 12 and 36 month follow-up. Underlying mechanisms of change are investigated. Statistical analyses will be conducted using the appropriate multilevel approaches, mainly two-level regression and growth analysis.

**Discussion:**

The results of this study will indicate whether the integration of emotion-focused elements into treatment as usual increases the effectiveness of Psychological Therapy. If advantages are found, which may be limited to particular variables or subgroups of patients, recommendations for a systematic integration, and caveats if also disadvantages are detected, can be formulated. On a more abstract level, a cognitive behavioral (represented by PT) and humanistic/experiential (represented by EFT) approach will be integrated. It must be emphasized that mimicking common practice in the development and continued education of psychotherapists, EFT is not integrated as a whole, but only elements of EFT that are considered particularly important, and can be trained in an 8-day training plus supervision of therapies.

**Trial registration:**

ClinicalTrials.gov, NCT02822443, 22 June 2016, retrospectively registered

## Background

Grawe formulated an approach designated General Psychotherapy [1–3] in which he postulated that first generation approaches, the original approaches to psychotherapy as developed by their founders, had to be overcome. In his opinion they neglect or even suppress and fight concepts and findings that are not in line with their original stance. Second generation approaches, in contrast, utilize all concepts and evidence relevant for a scope of applications. The domain for which it claims relevance may be limited, but all that is relevant to the claimed range of application should be integrated. As research is continually developing, *General Psychotherapy* stands for a continuous endeavor despite the end state never fully being reached. It is not just another approach to psychotherapy with a fixed set of concepts and interventions, but rather a model in continuous development. *Psychological therapy* (PT; [4, 5]) as practiced in Bern at the outpatient clinic of the Institute of Psychology and taught in the postgraduate training program as well as in many other German-speaking institutions, follows the idea of General Psychotherapy. It is mainly a cognitive behavioral approach that has its roots in humanistic and learning theories, but also relies on cognitive science, emotion and social psychology, neurobiology, and interpersonal and systemic approaches. Since its origins in the late 70’s, there has been an ongoing attempt to follow the principles of General Psychotherapy. This has led to an approach that could be described as integrative [6]. The integration, however, is not eclectic but guided by theoretical concepts such as general change factors [4]. These change factors include clarification, resource activation, problem activation, and problem mastery. Psychotherapeutic interventions can be related to these factors, which allows for the description of approaches to psychotherapy in terms of their typical profiles. Cognitive-behavioral therapy (CBT), for example, has an emphasis on mastery, and problem activation takes specific forms, such as behavioral exposure. Systemic approaches have a traditional strength in resource activation. Client centered therapy and psychodynamic approaches predominantly offer interventions fostering clarification, etc. A problem is that not all patients need the same profile in their therapy, and matching the patients’ needs with what a traditional approach has to offer is not an optimal solution: The same patient may need different approaches for different problems, there may be a change of needs over time, and not all relevant problems may be known in the beginning of a therapy. Therefore a psychotherapeutic approach should be adaptable to the patient needs and possibilities as reflected in a case formulation [7]. To reach this goal, it is desirable that for all change factors a sufficient range of interventions and concepts upon which they are based is available, and the use of each has been empirically studied.

In the past decades Emotion-Focused Therapy (EFT) has become increasingly popular, both in clinical practice and in research. EFT is an approach of humanistic, client-centered, and gestalt origin. Main proponents are Greenberg, Elliott, Paivio, Watson, Pascual-Leone, Goldman, and Pos (for an overview: [8]). EFT refers to common concepts of emotion psychology and other relevant domains of psychology and includes a number of concepts as well as interventions. EFT is a process-oriented approach that integrates an empathic relationship offer and process-directive interventions aiming to improve a patient’s ability to constructively deal with emotions [9]. According to the prescriptive concepts of EFT, various types of emotional experiencing/processing are distinguished, which require different interventions. Important distinctions are primary vs. secondary emotions (roughly: natural/spontaneous vs. transformed/distorted) and adaptive vs. maladaptive emotions (roughly: helpful vs. not helpful for satisfying one’s needs). It is assumed that a patient’s problems are often related to an inability to understand own emotions and thus an inability to derive appropriate responses. It can also be an inability to expose oneself to threatening or painful emotions, even though such exposure has a potential of fostering personal development. The overarching goal is to enable the patient to become asymptomatic and improve quality of life by transforming maladaptive emotions into adaptive emotions. The therapeutic procedure is led by “markers” (indicators for problems in emotional processing, but also for a patient’s readiness to work on emotional problems), which become visible/audible in the therapeutic process and indicate which therapeutic interventions are most promising under which circumstances. Within a relatively short time, EFT has acquired a sound scientific stance in several empirical studies [10]. It corresponds to APA (American Psychological Association) standards of empirically validated treatments for individual treatment of depression and for couples therapy, for which manuals have been developed [9, 11–13]. Moreover, there is evidence for positive effects on other disorders.

In practice, psychotherapists increasingly tailor their interventions to the characteristics of an individual patient and thereby use a number of methods not confined to a single therapy approach. Recent evidence shows that a big part, if not a majority of psychotherapists, adopt a rather integrative stance [14]. Trained in one approach, therapists seek complements in other approaches when they find conceptual and practical weaknesses of their initial approach. With experience, therapists acquire elements from other therapy schools and traditions and thus become more flexible in the treatment of their patients, conceptually and technically. Therapists tend to integrate therapeutic elements from a new approach into the old one, once they were found effective through empirical evidence. They rather integrate elements of a new approach into an old one than changing completely from the original approach to another [15]. At the level of training, a recent study conducted in the United States showed that one third of the accredited training programs in psychotherapy offer mandatory or optional training in five major psychotherapy theories (psychodynamic theory, humanistic theory, cognitive theory, behavioral theory, systems theory), 90% reported teaching psychotherapy integration in one or more courses [16]. The majority of trainees characterizes their therapeutic approach as “eclectic/integrative” [16], and in private practice, only two percent of therapists completely identify themselves with one single orientation [17]. A common type of integration has been named assimilative integration, that is, therapists are trained in a particular approach and take it as a point of departure for integrating other concepts and interventions that appear as particularly useful complements to the original one [15]. A recent expert panel on the future of psychotherapy in the United States of America (“Psychotherapy in 2022“) estimated a likely increase of integrative approaches [18].

Nevertheless, it is uncommon to study such integration, and research on its effects on process and outcome is rather rare [16]. Thus, more research on psychotherapy integration is needed, if psychotherapy research is to cover real practice in an endeavor to reduce the currently much bemoaned scientist-practitioner gap. The main aim of this study is to compare Psychological Therapy corresponding to the usual practice in Bern to Psychological Therapy with integrated EFT elements. A central characteristic of the presented project is its external validity being particularly evident in the elaboration of naturalistic conditions and treatment as usual (TAU) being part of both conditions (TAU + EFT and TAU). Twenty-three therapists per condition treat a total of 130 patients from the outpatient clinic of the University of Bern, suffering from depressive, anxiety and adjustment disorders. Therapists vary in their general therapy experience and extent of training. This will allow for evaluating the influence of these variables. To secure balance regarding the amount of training and supervision between the project conditions, TAU without EFT will be supplemented with additional units elaborating on some elements that are already part of PT.

The overarching question addressed is: What are the consequences of systematically integrating emotion-focused concepts and interventions into Psychological Therapy? This is seen as exemplary for major steps in therapy development in the sense of General Psychotherapy and follows suggestions by others [19]. The general research question can be subdivided into the following questions:Is there a general superiority of TAU + EFT over TAU in the changes from pre to follow-up (with indicators such as stability of change, post-therapeutic gain, and reduction of relapses)?Is there a superiority of TAU + EFT over TAU in variables indicating deeper levels of processing?Are there negative side effects of the integration e.g. due to less attention and time dedicated to more traditional but useful elements and procedures?Additional exploratory research questions include the examination of potential predictors, moderators and mediators of outcome (e.g. symptom severity, onset of primary disorder, previous psychotherapies, and process variables such as experiencing ratings).

Some questions are specific in terms of differential effects regarding TAU and TAU + EFT (e.g., level of experiential processing, emotion-regulation skills). The example of emotional processing (EP) is used to illustrate the kind of planned analyses. EP is assumed to be a trans-theoretical mechanism of change [20] and emotion-focused interventions are considered potent ways to facilitate emotional processing [12, 21]. Moreover, the level of EP has predicted psychotherapy outcome in previous research [22, 23]. Therefore, we hypothesize that patients in TAU + EFT will show higher levels of EP than patients in TAU, and the level of EP in both conditions will mediate the relationship between emotion-focused interventions and therapy outcome. Higher levels of EP will predict better outcomes at follow-up.

## Methods

### Participants

A total of 130 patients fulfilling the diagnostic criteria for a unipolar depressive (ICD, F32), anxiety (ICD, F40, F41) or adjustment disorder (ICD, F43.2) are being recruited, with 65 participants randomly assigned to the TAU + EFT condition and 65 to treatment as usual. Participants are recruited at the psychotherapy outpatient clinic of the University of Bern, once they have registered for therapy and meet the requirements for participation in the study. As both conditions can be offered as treatments with empirically supported effects, it is not expected that many patients will decline, although the standard of 25 ± 3 sessions may be an obstacle to some.

With an average of three therapies per therapist, 23 therapists are needed per condition. In support of external validity and generalizability of our findings, therapists of varying experience are included. The participation of five experienced therapists and 18 therapists in training per condition is planned. All therapists in this study have a master’s degree in psychology and therapists in training have been in postgraduate training at the University of Bern for at least 1 and a half years.

### Inclusion and exclusion criteria

One important goal of this project is to inform therapists about the effects of integrating emotion-focused elements in Psychological Therapy in a naturalistic and routine practice setting. To maximize external validity and generalizability to common therapeutic practice the patient sample should not be too homogeneous and the sample should be replicable. A good solution seems to focus on patients with unipolar depressive, anxiety and adjustments disorders as the most prevalent patient groups in psychotherapy outpatient settings [24], making about 50% of the patients in our outpatient clinic. Minimum age is 18. Exclusion criteria are active substance dependence for the previous 6 months, current suicidal risk or immediate threats of self-harm, or meeting criteria for organic mental disorders. In addition, we exclude individuals with health conditions that require medication potentially affecting their mood (e.g., steroids), and individuals receiving concurrent psychological treatments, including psychotherapy. Patients who have been under antidepressant medication at a stable dose for at least 1 month are allowed to participate. Comorbidity with disorders not on the exclusion list does not lead to exclusion as long as anxiety, depression, or adjustment problems are of primary concern.

### Sample size calculation

Based on a power analysis with G*Power [25] an optimal total sample size of 130 patients allows for the detection of a small effect (Cohen’s f = 0.10) for the interaction between time (pre, post, follow-up) and treatment condition (TAU + EFT vs. TAU) (repeated measures analyses of variance (ANOVA), within-between-interaction; *α* = 0.05; power = 0.80; number of groups = 2; number of measurements = 3; pre-post correlation of pre-post values: *r* = 0.6; non-sphericity correction = 1). Multilevel models allow for assessment-by-assessment approaches: Assuming 130 patients and three assessments per patient (pre, post, follow-up), the resulting N would be 390. Further assuming a 20% dropout rate at follow-up, this sample would be reduced to 312. This would enable the detection of small effects of 3.4% explained variance in a regression model (linear multiple regression: random model; H1: ρ2 > 0; α = 0.05; power = 0.80) with three predictors (treatment condition, time, and their interaction); and would still allow the identification of small effects of 5.1% explained variance in a model including additional covariates with a total of ten predictors [25].

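### The 80% power for the time-by-condition interaction needs all 130 randomised patients fully assessed; the protocol's own 20% dropout is never carried into it

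*Protocol article*

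**What the plan says.** Under Sample size calculation, the protocol article reports a G*Power result for a repeated-measures ANOVA: "an optimal total sample size of 130 patients allows for the detection of a small effect". The effect is Cohen's f = 0.10 for the interaction of time (pre, post, follow-up) with treatment condition, and the test is the "within-between-interaction". The other inputs are alpha 0.05, "power = 0.80; number of groups = 2; number of measurements = 3", a correlation of 0.6 between repeated measures and a non-sphericity correction of 1.

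The Participants section makes 130 the number randomised as well: "with 65 participants randomly assigned to the TAU + EFT condition and 65 to treatment as usual".

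A second calculation follows in the same section. It counts assessments (130 × 3 = 390) and then brings in attrition: "Further assuming a 20% dropout rate at follow-up, this sample would be reduced to 312". From 312 it derives detectable explained variances of 3.4% (three predictors) and 5.1% (ten predictors) in a multiple regression.

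The Analysis section plans multilevel models over pre, post and 12-month follow-up, with multiple imputation, in all randomised patients who attended at least one session. The arms are compared over time through a cross-level interaction of time and condition.

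**The concern.** The same number, 130, serves as the count of patients randomised and as the count of fully assessed patients that the power calculation needs. Both cannot hold if one patient in five is lost by follow-up, which is what the section itself assumes. The interaction is the contrast on which the arms are compared, and its power after dropout is not given anywhere.

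The regression figure does not fill the gap. It tests whether three predictors together (condition, time and their interaction) explain any variance. Patients who improve equally in both arms could satisfy that test through time alone. It also treats the repeated assessments as the sample size.

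What is at stake is how a null result will be read. Both arms are active treatments, and the Discussion notes that component studies have rarely found much difference, so a null result is a realistic outcome. Readers will judge it against the stated power and effect size. They therefore need the power that applies after the expected attrition, and the effect on a scale they can interpret.

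**Working it through.** **Inputs** (Sample size calculation, except where noted): f = 0.10; m = 3 measurements; k = 2 groups; r = 0.6; ε = 1; α = 0.05; N = 130, 65 per arm (Participants); dropout 20%.

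**1. Reproducing the stated figure.** Noncentral F in G*Power's default form:

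λ = f² × N × m × ε / (1 − r), df1 = (k − 1)(m − 1) = 2, df2 = (N − k)(m − 1).

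- N = 130: λ = 0.01 × 130 × 3 / 0.4 = 9.75; df 2 and 256; power 0.8001.
- N = 128: λ = 9.60; df 2 and 252; power 0.793.

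The figure reproduces, and 130 is the smallest equal-arm total that reaches 80%. There is no reserve.

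**2. Applying the protocol's own dropout.** The cut from 390 to 312 is 104 × 3, so it is equivalent to 130 × 0.8 = 104 patients with all three assessments.

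- N = 104: λ = 0.01 × 104 × 3 / 0.4 = 7.80; df 2 and 204; power 0.699.
- Effect detectable with 80% power at N = 104: f = 0.112.
- For reference, keeping 130 complete patients would mean randomising 130 / 0.8 = 162.5, so 163, or 164 for equal arms.

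**3. Allowing for partial data.** The planned analysis does not discard incomplete patients, so the complete-case figure is a lower bound within this set of assumptions. Assume compound symmetry with r = 0.6, data missing at random, no therapist clustering, and per arm 52 complete patients plus 13 incomplete ones. The information for the three arm means is summed over patients. The 2-df interaction contrast δ then gives λ = δ′(CVC′)⁻¹δ, where V is the covariance matrix of the between-arm differences and C takes post minus pre and follow-up minus pre. Each pattern is scaled so that f = 0.10.

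| Between-arm difference at pre, post, follow-up | Only follow-up lost: λ, power | Post and follow-up lost: λ, power |
|---|---|---|
| 0, d, d (maintained) | 9.30, 0.78 | 8.24, 0.72 |
| 0, d/2, d (linear) | 8.39, 0.73 | 8.13, 0.72 |
| 0, 0, d (follow-up only) | 7.93, 0.71 | 7.91, 0.71 |
| 0, d, 0 (post only) | 9.30, 0.78 | 7.91, 0.71 |
| 0, d, d/2 (half faded) | 9.75, 0.80 | 8.13, 0.72 |

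The range is 71% to 80%. The upper end needs an effect that has half faded by follow-up and a post value for every patient.

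**4. The regression figure.** With N = 312, the tests of 3.4% (three predictors) and 5.1% (ten predictors) have power of about 0.79 to 0.80, so these figures reproduce too. They concern the whole model and say nothing about the power of the interaction.

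**5. What f = 0.10 means between arms.** With within-cell SD 1 and between-arm differences D_t, f² = mean of (D_t − D̄)² / 4.

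- Maintained (0, d, d): mean squared deviation 2d²/9, so f² = d²/18, f = 0.2357d, and f = 0.10 gives d = 0.424.
- Linear (0, d/2, d): mean squared deviation d²/6, so f² = d²/24, f = 0.2041d, and f = 0.10 gives d = 0.490.
- At f = 0.112 (80% power on 104 complete patients): d = 0.475 and 0.548.

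The protocol states no time pattern, so the choice of pattern is an assumption.

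**The case against.** The stated sentence is correct as a calculation: with the listed inputs, 130 patients give 80%, and the text does not claim that this figure survives dropout. Nor does the section ignore attrition, since it allows for it in the calculation offered for multilevel models. This stands, and it limits the defect to an allowance that was not carried over to the interaction test.

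A reader might infer that the trial simply has 70% power. The documents do not support that. The 70% belongs to a repeated-measures ANOVA on complete cases, whereas the Analysis section plans multilevel models with imputation in a modified intention-to-treat set. Dropout placed at follow-up most naturally leaves the pre and post values observed. The symptom scales are also collected at sessions 8 and 16 and at other follow-ups, and imputation might use them; the article does not say whether it will. Still, even the favourable case stays below 80% for most patterns. Several of the patterns of direct interest, such as gains after therapy, are the ones that lose most.

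A reader might also infer that calling the effect small is an error. It is not: f = 0.10 is small by the ANOVA convention, and the metric is printed beside the word. The protocol claims no power for a 0.20 SD difference. The equivalent in SD units helps the reader; it does not correct a mistake.

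**Conclusion.** The point holds in a limited form. The 80% is conditional on no loss at any of the three assessments, while the same section expects 20% loss and applies it only to a calculation that does not test the interaction. After that loss, power for f = 0.10 lies between about 70% (104 complete cases) and 80% (partial data kept, most favourable pattern).

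The complete-case figure rests only on the protocol's inputs. The 71% to 80% range also needs the assumptions in step 3, and the SD equivalents need an assumed time pattern. It does not follow that the sample size was computed wrongly, or that N must rise. This is a disclosure point that should be fixed before results are reported.

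**What to change.** Keep N = 130 and restate the power along these lines:

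*With 130 patients randomised and 20% lost by follow-up, power for f = 0.10 on the interaction is about 70% on 104 complete cases (80% power needs f = 0.112). It is roughly 71% to 80% if the planned multilevel and imputation analysis keeps partial data, assuming compound symmetry, r = 0.6, data missing at random and no therapist clustering, and depending on the pattern of the effect over time.*

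The label of a small effect can stay. Beside it, add that f = 0.10 here corresponds to a between-arm difference of about 0.42 SD if maintained or 0.49 SD if it grows linearly, and that 80% power on 104 complete cases needs about 0.48 to 0.55 SD, with the time pattern named as an assumption. State that a null result will be interpreted by its confidence interval.

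The cost is wording only. Recruitment, design and analysis are unchanged; the stated power becomes less favourable. The Trial status section reports 28 patients recruited, so the statement could be corrected well before outcome data are analysed.

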
## Discussion

In this randomized controlled trial, the effectiveness of treatment as usual with integration of emotion-focused components (TAU + EFT) and TAU is compared. The originality of this project lies in the examination of the consequences of integrating interventions of another promising evidence-based approach (EFT) into treatment as usual in a way that is directly mirroring common integrative practice. The use of an elaborated and intensively used psychotherapeutic model (TAU) speaks for a general effectiveness of both conditions. Emotion-Focused Therapy has acquired empirical validation for the treatment of depression, trauma and abuse [12]. Clinically significant improvements with substantial effect sizes for both treatments in primary and secondary outcome measures are thus expected.

Other projects dealing with the integration of EFT elements [12, 22, 23, 58] did not report great differences in effectiveness. Newman and colleagues for example [58] compared an integrative psychotherapy of generalized anxiety disorder that added EFT and interpersonal elements to a standardized CBT treatment with a treatment that added supportive listening to the same CBT component. The integrative therapy was equally effective post treatment and 2 years later, so that the authors concluded that the augmentation of CBT with emotion-focused and interpersonal techniques might not lead to better outcomes for generalized anxiety disorder patients. Similar results were found in an RCT on the treatment of patients with depression by Grosse Holtforth et al. [22], comparing Exposure-Based Cognitive Therapy (EBCT) with CBT. Component studies, which look at the effects of either adding particular techniques to a form of therapy (additive design) or taking them away (dismantling studies) rarely find that the presence or absence of specific techniques makes much difference to the overall outcomes [57]. In the history of psychotherapy, there are many examples of interventions that were less effective than expected, showed negative side effects, and worked in a different way than was believed [59, 60].

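### The supplementary regression figures (3.4% and 5.1% explained variance at N = 312) do not state power for the treatment comparison, and the ANOVA calculation that does has no dropout allowance

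*Protocol article*

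**What the plan says.** The Sample size calculation section of the protocol article contains two calculations.

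- **Repeated-measures ANOVA.** Its target is the time-by-condition interaction: f = 0.10, two groups, three measurements, correlation 0.6, α = 0.05, power 0.80, giving 130 patients. The Participants section splits them equally, "with 65 participants randomly assigned to the TAU + EFT condition and 65 to treatment as usual".
- **Regression, offered for the multilevel models.** "Assuming 130 patients and three assessments per patient (pre, post, follow-up), the resulting N would be 390". Then: "Further assuming a 20% dropout rate at follow-up, this sample would be reduced to 312". The result: "This would enable the detection of small effects of 3.4% explained variance in a regression model". The test is specified as "linear multiple regression: random model; H1: ρ2 > 0", "with three predictors (treatment condition, time, and their interaction"), and 5.1% is given for ten predictors.

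The Analysis section plans multilevel models because a patient's observations are not independent. It uses a modified intention-to-treat set (randomised, at least one session) with multiple imputation, and examines the treatment difference in change as a cross-level condition-by-time interaction. The Discussion adds: "Clinically significant improvements with substantial effect sizes for both treatments in primary and secondary outcome measures are thus expected".

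**The concern.** The regression sentences are the only place in the section where dropout is considered, and they assure the reader that small effects remain detectable after it. Three features undermine that assurance.

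1. The hypothesis concerns all predictors jointly, and time is one of them. The authors expect large change over time in both arms, so the test can succeed when the arms do not differ.
2. Assessments are entered as if each came from a different patient, although the preceding sentence assumes a within-patient correlation of 0.6.
3. Dropout is placed at follow-up but deducted from all three time points.

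What is at stake is the reading of a null result, a live possibility because the Discussion reports that related studies found little difference between treatments. A reader who relies on 3.4% would credit the trial with a sensitivity to arm differences that this calculation does not establish.

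**Working it through.** **Inputs.** From the Sample size calculation section: 130 patients, three assessments, 20% dropout at follow-up, r = 0.6 (stated for the ANOVA), f = 0.10, α = 0.05, power 0.80, three or ten predictors. The sizes of common improvement below are assumptions.

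**1. Reproducing the stated figures.** The omnibus F test has p and N − p − 1 degrees of freedom. Under the random-predictor model the noncentrality is ρ²/(1 − ρ²) × χ²(N − 1), averaged over the χ². With N = 312 independent units, the ρ² detectable at power 0.80 is 3.45% (p = 3) and 5.14% (p = 10). At the stated 3.4% and 5.1% the power is 0.794 and 0.796. So the plan's figures are those of the omnibus test with 312 assessments counted as 312 independent subjects.

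**2. What that test detects when the arms are identical.** Take an improvement of s SD from pre to post, held at follow-up, the same in both arms, with time entered linearly.
- Variance of the three means: s² × 2/9. A linear time term captures 75% of it, so R² = 0.75 × (2s²/9) / (1 + 2s²/9).
- s = 0.5: R² = 0.0417/1.0556 = 3.9%; power at N = 312 is 0.86.
- s = 0.8: R² = 0.1067/1.1422 = 9.3%; power is 0.999.

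If the change is instead linear from pre to follow-up, a common shift of 0.46 SD alone explains 3.4%. As a check, 130 patients were simulated with r = 0.6, 26 follow-ups missing and no arm difference, ignoring the clustering. The omnibus test rejected in about 97–98% of runs for a common change of 0.5 SD and in 100% for 0.8 SD.

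**3. Direction of the independence error.** In the same simulations, tests that ignore clustering rejected the true null, against a nominal 5%:
- arm main effect: about 17% (anticonservative);
- condition-by-time interaction: about 0.4% (conservative).

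**4. The dropout count.** 20% of 130 is 26, so 130 + 130 + 104 = 364 assessments remain. The figure 312 is 0.8 × 390, or equivalently 104 × 3, that is, completers only. On the plan's own method, 364 independent units would give 2.96% and 4.41%, so this slip alone makes the stated figures slightly pessimistic.

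**5. The ANOVA calculation.** λ = N × m × f²/(1 − r), with df 2 and 2(N − 2).
- N = 130: λ = 130 × 3 × 0.01/0.4 = 9.75, df 2 and 256, power 0.800. The stated figure reproduces.
- N = 104: λ = 104 × 3 × 0.01/0.4 = 7.80, df 2 and 204, power 0.699.

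**6. An approximate detectable arm difference at 12 months.** Simple two-arm contrast, 104 observed, r = 0.6: d = 2.80 × √(4v/104).
- Baseline-adjusted, v = 1 − 0.6² = 0.64: d = 0.44.
- Change score, v = 2(1 − 0.6) = 0.80: d = 0.49.

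**The case against.** The strongest defence is that nothing depends on these figures. The section opens with a calculation for the planned contrast, and it is right at N = 130. This stands: the sample size does not rest on the regression figures, and the section as a whole does address the interaction. But that calculation has no attrition allowance, and the sentences that appear to supply one do not test the interaction.

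A second defence is that 312 is a cautious choice. It is pessimistic as a count, and three assessments on each of 104 completers would yield it. That reading still conflicts with the modified intention-to-treat set, and a cautious N does not change which hypothesis is tested.

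Two stronger readings are tempting.

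- A reader might infer that counting assessments as patients inflates the apparent power for the treatment contrast. The planned contrast is a within-patient interaction, for which ignoring the correlation is conservative. Precision is overstated only for between-patient effects: the arm main effect and patient-level covariates.
- A reader might infer that the truly detectable explained variance is about double the stated values. That applies a between-patient design effect to a model in which time and the interaction vary within patients. For between-patient predictors only, 364 assessments (2.8 per patient on average) have a design effect of 1 + 1.8 × 0.6 = 2.08 and an effective N of 175, giving 6.1% and 9.1%. Even this carries over an r stated only for the ANOVA.

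**Conclusion.** The point holds for the supplementary regression figures. They are not valid statements of power for the treatment comparison, chiefly because improvement common to both arms can satisfy the omnibus test; that reason suffices by itself. The independence assumption and the dropout count are further errors, but they do not all act in one direction. The documents do not support saying that the trial's sample size is miscalculated or that no power for an arm difference is stated.

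The remaining weakness is that power for f = 0.10 falls from 0.80 to about 0.70 if only 104 patients contribute complete data. This rests on the plan's own r = 0.6 and sphericity. It is best read as a lower bound under those assumptions, since the planned analysis keeps the earlier assessments of patients lost at follow-up. The 0.86 to 0.999 range rests on assumed gains of 0.5 to 0.8 SD; the protocol says only that substantial effects are expected. This should be fixed, but it alters no estimand, test, analysis set or allocation.

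**What to change.** Delete the 390/312 regression figures. In their place, state power or the detectable effect for the condition-by-time contrast itself, with 20% missing at 12 months. Either of these would serve:

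- power of about 0.70 for f = 0.10 with 104 completers, given as a lower bound under the ANOVA assumptions;
- a detectable difference at 12 months of about d = 0.44 (baseline-adjusted) to 0.49 (change score), with 104 observed and r = 0.6, labelled as an approximation from a simple two-arm contrast and not as a property of the planned multilevel model.

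If therapist clustering is added, label the intraclass correlation as an assumption, since the article gives none. If a precision statement for patient-level covariates is wanted, confine it to between-patient predictors and base it on 364 assessments.

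The cost is one rewritten paragraph and no change in enrolment. The stated sensitivity becomes less favourable.
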